#### 3.1 Sample Size

Following protocol amendment 5, the sample size was increased from 90 to up to 120 patients in order to provide 90 who would meet the per protocol criteria and be evaluable for the primary efficacy analysis. Furthermore, this protocol amendment also specified that patients who had potentially received insufficient or incorrect study medication may be replaced.

If the standard deviation is approximately half (53%) of the mean difference in the maximum MCA flow velocity, 90 evaluable patients will have 80% power to detect a statistically significant difference between treatment arms using a 1-sided type 1 error rate of 5%. Statistical significance will be declared if the 2-sided p-value is  $<0.05$ , in this case the trial will have  $>80\%$  power with 90 evaluable patients if the standard deviation is  $<59\%$  of the mean difference.

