**Table 1. TCD Recordings**

| Reading                                           | Units/Response |
|---------------------------------------------------|----------------|
| Left Middle Cerebral Artery Mean Flow Velocity    | cm/s           |
| Right Middle Cerebral Artery Mean Flow Velocity   | cm/s           |
| Left Internal Cerebral Artery Mean Flow Velocity  | cm/s           |
| Right Internal Cerebral Artery Mean Flow Velocity | cm/s           |
| Assessment Performed                              | Pre/Post       |
| Lindergaard Ratio Left                            | none           |
| Lindergaard Ratio Right                           | none           |

The primary endpoint is defined as the maximum of all left middle cerebral artery mean flow velocities (MCA-MFV) and right MCA-MFV values recorded after the first dose of randomised therapy including any taken after Day 7.

Baseline values will be defined as:

- The lowest of the left and right MCA-MFV values recorded at the earliest TCD assessment made within 2 days of first dose
- If a patient does not have a TCD recorded within 2 days of dosing, a predicted baseline value will be imputed based on their age, WFNS score (1 to 5), a past medical history of hypertension (yes/no), surgical procedure (clipping, coiling, none), log-CRP and centre as described below.

Amongst patients with baseline values recorded within 2 days of dosing, their baseline value will be regressed on age, WFNS score, hypertension, surgical procedure, log-CRP and centre. The imputed value for patients with a missing baseline value will equal  $\mu + \sum x_{ij}\beta_j$  where  $x_{ij}$  represent the observed values of the  $j$  covariate levels for the  $i^{\text{th}}$  patient and  $\beta_j$  the corresponding parameter estimates from the regression amongst patients with observed baseline values.

Supplementary analyses will also be performed on the mean of the three largest right or left MCA-MFV recorded at any timepoint after dosing. Additionally, an analysis will be performed to describe the effect over time with timepoints grouped, relative to date of Ictus, as Days 3-4, 5-6, 7-9, 10-14, 15-21, 22-28. Within each timepoint the largest MCA-MFV value will be included in the analysis for each patient. For these two analyses, the same baseline as the primary analysis will be used. Using the timepoint analysis the mean effect of Days 5 to 9 will also be estimated.

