## 6 Statistical Methods

### 6.1 General Considerations

All data will be described and analysed according to treatment arm (SFX-01, Placebo) and day and time of assessment (if appropriate), for each patient population (PP, ITT, Safety, sub-study PK).

A (two-sided) significance level of 5% ( $<0.05$ ) will be implemented throughout. The null hypothesis assumed throughout is that there is no difference between the active treatment and the control for any comparison performed (SFX-01 vs Placebo).

Part way through the trial the randomization was amended to stratify by WFNS score (1-3 v 4-5) and centre. For purposes of analyses that are stratified, WFNS score will be taken from the CRFs for patients randomized prior to the amendment and from the random scheme for patients randomized after the amendment.

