| Blood & CSF HP and MDA       | Blood concentrations of HP & MDA at Day 7 and D28
CSF concentrations of HP & MDA at Day 7                                                                                                                                                                                                                                                                       |

Analyses of the TCD, mRS and GOSE endpoints will be performed in both the PP and ITT populations with the PP population considered as primary. Other endpoints will initially only be analysed in the PP population and will only be analysed in the ITT population if there is a meaningful discrepancy in the results of endpoints analysed in both populations.

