## 6.5 Analysis of Secondary Efficacy Endpoints

The mRS, GOSE, SAHOT and CLCE will be analysed using a proportional odds logistic regression model to each timepoint separately including the following covariates: treatment, age (fitted as continuous variable), WFNS score (fitted as a class variable), hypertension (yes vs no), surgical procedure (clipping vs coiling vs none) and log-CRP. The treatment effect will be described using an odds ratio together with its likelihood ratio based 95% confidence interval. The statistical significance of the treatment effect will be taken from the chi-square test for the difference in deviance when removing treatment from the model. GOSE scores will be reversed prior to analysis so the odds of a better response is being modelled. PROC LOGISTIC can be used to analyse the data. If the model does not converge, any covariates that are not statistically significant will be removed in order from least significant until the model converges. If the model still does not converge, the outcome level with the fewest observations will be combined with the next most severe outcome and this process repeated until convergence is achieved.

BICRO and SF-36 will be analysed using Van-Elteren's test with 4 strata defined by age (above and below the median) and WFNS score (1-3 v 4-5). The treatment effect will be described using an un-stratified Hodges-Lehmann (HL) estimate of median difference together with its 95% confidence interval. The test can be implemented in SAS as follows:

```

proc npar1way data=data1 HL;
  strata strata/wilcoxon;
  class trt;
  var resp;
run;

```

The proportion of patients with delayed cerebral ischaemia, new cerebral infarct and receiving triple H therapy will be analysed using logistic regression with the same set of covariates used for mRS. The statistical significance of the treatment effect will be taken from the chi-square test for the difference in deviance when removing treatment from the model. The treatment

effect will be described in terms of an odds ratio together with its likelihood ratio based 95% confidence interval.

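### The likelihood ratio tests for DCI, new infarct and Triple H fit too many parameters for the likely number of events, and run at about 6.5-9.5% rather than 5% over assumed event rates of 10-40%

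*SAP*

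**What the plan says.** Section 6.5 states that the three binary endpoints "will be analysed using logistic regression with the same set of covariates used for mRS". The mRS list begins with "treatment, age (fitted as continuous variable"), continues with "WFNS score (fitted as a class variable"), and adds hypertension, surgical procedure at three levels and log-CRP. Treatment is tested by the change in deviance on removing it, referred to chi-square, and the odds ratio carries a likelihood-ratio 95% interval.

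Section 6.1 sets a two-sided "significance level of 5"% for all comparisons. On the population, the text after Table 11 (Section 6.2) says "Other endpoints will initially only be analysed in the PP population". Section 3.1 explains that recruitment was enlarged "in order to provide 90 who would meet the per protocol criteria".

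Section 6.5 has a rule for models that do not converge: drop non-significant covariates, then merge outcome levels. It stands in the paragraph on the proportional odds models and is not repeated for the binary endpoints. The SAP gives no expected event rates for these endpoints and no penalised or exact alternative.

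**The concern.** The chi-square reference for a deviance difference is a large-sample result. It needs enough events per fitted parameter, and a rare binary outcome in 90 patients may not supply them. The test then rejects too often when there is no effect. Because the interval inverts the same test, it covers less than 95%.

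Reducing DCI is a named secondary objective (Section 2). Section 6.9 justifies the move to covariate models by greater power and by estimates with intervals. If the test does not hold its level, part of that apparent gain is false-positive error.

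**Working it through.** **Slopes.** Treatment 1, age 1, WFNS 4, hypertension 1, surgery 2, log-CRP 1: 1 + 1 + 4 + 1 + 2 + 1 = 10. With WFNS at two levels: 1 + 1 + 1 + 1 + 2 + 1 = 7. Section 6.5 does not state the number of WFNS levels. Five is the natural reading: Section 5.1 gives "WFNS score (1 to 5"), and Section 6.5 itself writes out the 1-3 v 4-5 split for the Van Elteren strata, where two are meant.

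**Events.** Events = 90 × rate. At 10/20/30/40% that is 9/18/27/36 events, or 0.9/1.8/2.7/3.6 per slope with ten slopes.

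**Simulation.** The plan's figure to reproduce is the nominal 5%. Inputs from the SAP: N = 90, the covariate list, the deviance test on 1 df, two-sided 5%. Assumptions, because the SAP gives none of these:
- event rates 10-40% and 1:1 allocation;
- WFNS grades 1-5 at 40/20/8/17/15%, with a sparser variant at 50/20/4/13/13%;
- surgery levels 70/20/10% and hypertension 30%;
- standard normal age and log-CRP;
- covariates either unrelated to outcome or moderately prognostic.

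For each of 8,000 null trials per setting, D = deviance without treatment − deviance with treatment, rejecting when the chi-square (1 df) p-value is below 0.05. The Monte Carlo standard error is √(0.07 × 0.93 / 8,000), about 0.3 points.

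Ten slopes, ordinary likelihood:

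| Event rate | Events per slope | Type I error, prognostic | Non-prognostic | Sparser WFNS grade 3 | Trials with (quasi-)separation, prognostic |
|---|---|---|---|---|---|
| 10% | 0.9 | 9.5% | 8.5% | 9.3% | 83% |
| 15% | 1.35 | 7.8% | 7.5% | 7.8% | 61% |
| 20% | 1.8 | 7.8% | 7.0% | 7.4% | 41% |
| 25% | 2.25 | 7.1% | 6.7% | 6.9% | 27% |
| 30% | 2.7 | 7.1% | 6.9% | 6.9% | 18% |
| 40% | 3.6 | 7.2% | 6.7% | 7.2% | 9% |

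A separate simulation gave 9.0/7.5/6.6/7.0% at 12/20/30/40%. With N = 120 the range is still 6.3-8.1%.

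**Where the excess comes from.**
- The unadjusted likelihood ratio test on the same data runs at 4.6-6.3%, so most of the excess comes with the covariates.
- Two-level WFNS (7 slopes) still gives 6.0-7.9%, so grouping WFNS removes only part of it.
- A three-slope model (treatment, age, two-level WFNS) gives 6.1/5.2/5.9/6.0% at 10/20/30/40%.

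**Where separation sits.** Separation in the treatment term itself occurs in at most 2.6% of trials at a 10% event rate and in about 0% from 20% upward. The rest is in a sparse WFNS grade or the no-procedure level.

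**Interval.** Under no effect, coverage is 100% minus the test size: about 92-93.5% at event rates of 20-40%, and 90.5-92% near 10-12%.

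**Firth penalised likelihood, same ten slopes.** The penalised likelihood ratio test gives 3.7/4.3/5.1/5.5% at 10/20/30/40% (4,000 trials each). A separate run gives 5.2/4.8/4.8/5.2% at 12/20/30/40%. Estimates are finite.

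**The case against.** **Five-level WFNS is inferred.** The SAP does not state it for this model, and the code in Section 6.4 puts WFNS in a CLASS statement where it has two levels. This stands. A reader might infer that five-level coding is the cause, given that the randomisation was changed to "stratify by WFNS score (1-3 v 4-5) and centre". The figures do not support that: with two levels most of the excess remains.

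**Separation does little harm to the reported result.** This also stands. A reader might take the high separation rates to mean that the treatment odds ratio is often infinite or undefined. An infinite coefficient on a WFNS grade leaves the treatment estimate, its test and its profile interval defined. The separation rates therefore do not measure damage to the treatment comparison.

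**The existing non-convergence rule may help.** Extended to these models and triggered by separation, dropping covariates gives 7.1% instead of 8.8% at a 12% event rate, 6.8 v 7.2% at 18%, 7.6 v 7.8% at 25% and 5.7 v 5.8% at 35% (2,500 trials each, standard error about 0.5 points). It trims the top of the range without restoring 5%. Its second step, merging outcome levels, cannot apply to a two-level outcome.

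**The size depends on assumptions.** The 9% end needs an event rate near 10-12%, and the lowest single result, 5.8% at 35%, is close to nominal.

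**The consequence is limited.** The study title calls the efficacy evaluations exploratory. Section 6.3 makes no multiplicity adjustment among secondary endpoints and names mRS and GOSE at 90 days as the key ones. Of these three endpoints, only DCI is a named objective. That argues for moderate priority; it does not make the test valid at 5%.

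**Conclusion.** The point holds. Under ordinary maximum likelihood with ten slopes on about 90 patients, the tests of DCI, new infarct and Triple H run at about 6.5-8% at event rates of 20-40% and at about 8-9.5% near 10-12%, with intervals too narrow to match. The main cause is the number of parameters relative to events; WFNS coding is a minor contributor.

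The result rests on assumed event rates and covariate frequencies. The direction was the same at every rate tried, but the exact size is not known from the SAP. The documents do not support a wider conclusion that the treatment odds ratios will usually break down or that the primary TCD result is compromised. This should be corrected, as a matter for secondary endpoints.

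**What to change.** In Section 6.5, analyse the three binary endpoints by Firth penalised logistic regression with the planned covariates. Take the p-value from the penalised likelihood ratio test: twice the difference in penalised log-likelihood between the full fit and the fit with the treatment coefficient held at zero. Report the penalised profile-likelihood 95% interval. State the number of WFNS levels. Estimates are then finite, so no covariate-dropping rule is needed for separation in these models.

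Grouping WFNS as 1-3 v 4-5, to match the primary model and the randomisation strata, is optional. It saves three slopes, but grouping alone is not a remedy.

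The cost is a sentence or two in the SAP, a standard software option and slight shrinkage of the odds ratio towards 1. At an event rate near 10% the penalised test may be a little conservative (3.7% in one run, against 5.2% at 12% in another).

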## **6.6 Analysis of Pharmacokinetic Endpoints**

Blood concentrations, loge-transformed prior to analysis, of HP & MDA at Day 7 and D28 will be analysed by MMRM using the same model as described in the analysis of TCD data. Both EVD and non-EVD data will be included in the same model. This model will be used to derive separate treatment effects at Day 7 and Day 28. The baseline term in the models will be the blood concentrations recorded between pre-dose and 48h. A separate summary of the baseline concentrations will confirm that no treatment effect has emerged by 48h by summarising data according to whether data were collected pre-dose, within 24h and between 24 and 48h after dosing. If there is evidence of an effect within 48h, the nominal baseline values will be fitted as a separate visit and a covariate added indicating whether the patient had an EVD sited or not.

Loge-transformed CSF concentrations of HP & MDA at Day 7 will be analysed using an ANCOVA model with a 2-level covariate denoting whether the CSF values were taken from an EVD or lumbar puncture (LP). A treatment-by-covariate (EVD vs LP) interaction will be added to assess whether the effect of SFX-01 differs by whether the CSF was obtained from EVD or LP together with subgroup analyses for EVD and LP patients separately.

In all cases, the treatment effect will be presented as the ratio of glsmeans and associated 95% confidence interval having exponentiated the lsmeans and confidence limits calculated on the loge-scale.

Other pharmacokinetic measurements will be summarised only.

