### Secondary:

To determine if a minimum of 7 days treatment with SFX-01 improves clinical outcome following SAH as measured using the modified Rankin Scale assessed at 7 days, discharge, 28, 90 and 180 days post ictus.

To determine blood SFN levels (and its metabolites) with treatment with SFX-01 (300mg bid).

To determine CSF SFN levels and kinetics with treatment with SFX-01 (300mg bid).

To determine if up to 28 days treatment with SFX-01 increases blood haptoglobin (HP) levels and decreases malondialdehyde (MDA) levels following SAH.

To determine if up to 28 days treatment with SFX-01 can reduce the incidence of Delayed Cerebral Ischaemia (DCI) following SAH.

To determine if up to 28 days treatment with SFX-01 improves long-term outcome in subjects following SAH.

To determine if up to 28 days of treatment with SFX-01 can reduce iron deposition and cortical atrophy following SAH.

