### **6.4 Analysis of the Primary Endpoint**

All TCD endpoints will be  $\log_e$ -transformed prior to analysis including baseline values. The primary endpoint of maximum post-dose MCA mean flow velocity will be analysed using an Analysis of Variance (ANOVA) model with terms for treatment, baseline (as defined in Section 5.1), WFNS grade (1-3 v 4-5), hypertension (yes vs no), surgical procedure (clipping vs coiling vs none), log-CRP and age fitted as a continuous covariate. The statistical significance of treatment will be based on type III sums of squares. The supplementary analyses of the mean of the 3 largest post-dose MCA mean flow velocities and the maximum post-dose Lindergaard ratio will use the same methods.

The maximum MCA mean flow velocity per timepoint will be analysed using a mixed model repeated measures (MMRM) approach with visits grouped, relative to date of Ictus, as Days 3-4, 5-6, 7-9, 10-14, 15-21, 22-28 and baseline covariates as defined for the primary analysis. Treatment effects for each visit will be obtained from the same model using the corresponding treatment-by-visit estimate. The MMRM will include terms for treatment, visit, treatment-by-visit, baseline-by-visit, covariates and observations blocked by subject. An unstructured covariance matrix will be used to model the within-subject error, along with restricted maximum likelihood and the Kenward-Roger approximation to estimate the degrees of freedom. If the model will not converge with an unstructured covariance matrix, heterogeneous Toeplitz and Toeplitz patterns will be tried in that order until the model will converge.

An example of the corresponding SAS code is given below

```
PROC MIXED data=data1 method=reml;
  CLASS trt vis pat wfns htn surg;
  MODEL lnTCD=base trt vis trt*vis base*vis age wfns htn surg lcrp / ddfm= KR;
```

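### The blood HP and MDA models adjust for a baseline that may be taken up to 48 h after dosing; this takes out part of any early drug effect, and the remedy waits on an undefined trigger

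*SAP*

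**What the plan says.** Section 2 of the SAP lists a secondary objective that treatment "increases blood haptoglobin (HP) levels and decreases malondialdehyde (MDA) levels following SAH". Table 11 puts blood HP and MDA at Day 7 and Day 28 among the formal analyses.

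Under Section 6.6, the log-transformed blood concentrations "will be analysed by MMRM using the same model as described in the analysis of TCD data". Section 6.4 describes that model: "The MMRM will include terms for treatment, visit, treatment-by-visit, baseline-by-visit, covariates and observations blocked by subject". The baseline therefore has its own slope at each visit.

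Section 6.6 then fixes the covariate: "The baseline term in the models will be the blood concentrations recorded between pre-dose and 48h". The following sentence shows that the 48 h counts from dosing: "A separate summary of the baseline concentrations will confirm that no treatment effect has emerged by 48h", done by "summarising data according to whether data were collected pre-dose, within 24h and between 24 and 48h after dosing".

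The remedy is conditional: "If there is evidence of an effect within 48h, the nominal baseline values will be fitted as a separate visit", with an indicator for an external ventricular drain (EVD) added. The SAP gives no definition of evidence, no test and no threshold. It plans neither the alternative model nor a pre-dose-only covariate unconditionally.

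**The concern.** Treatment is twice daily (Section 3), so a sample at 48 h can follow about four doses (0, 12, 24 and 36 h). Such a value is not a baseline. It is a post-randomisation measurement of the marker that is also the outcome, and the drug may already have moved it. Adjusting for it removes some of that movement from the Day 7 and Day 28 comparisons. When early and late effects share a direction, the reported ratio is pulled toward 1.

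The safeguard is a descriptive table that the text expects to confirm the absence of an effect. A small table that shows no difference confirms nothing. The choice of model also depends on a by-arm look at the data with no rule for reading it. At stake is the size, and possibly the detection, of the effect on two markers named in a secondary objective.

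**Working it through.** The SAP gives no effect size, SD, baseline slope, share of post-dose baselines or power for HP and MDA, so there is no figure of its own to reproduce. The check shows how the bias works and how large it could be.

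**Inputs from the SAP**
- Baseline window, model and trigger: Sections 6.4 and 6.6, as quoted.
- Two-sided 5% level: Section 6.1.
- 90 evaluable patients: Section 3.1. Taking 45 per arm assumes equal allocation, which the SAP does not state.

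**Assumed inputs (SD units on the log scale)**
- D, the true later effect: 0.59, which 45 per arm detect with 79.9% power in an unadjusted two-sided 5% test.
- e, the true early effect in post-dose baselines.
- f, the fraction of baselines taken post-dose.
- b, the within-arm slope of outcome on baseline.

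**Step 1: bias.** The adjusted effect is the difference in outcome means minus b times the difference in covariate means. The expected covariate difference is f·e, so

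adjusted effect = D − b·f·e, and share lost = b·f·(e/D).

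This holds at each visit with that visit's slope.

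**Step 2: share of the later effect lost**

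| b | f | e/D = 0.25 | e/D = 0.5 | e/D = 1 |
|---|---|---|---|---|
| 0.3 | 0.5 | 4% | 7.5% | 15% |
| 0.5 | 0.8 | 10% | 20% | 40% |
| 0.7 | 1.0 | 17.5% | 35% | 70% |

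The central case is 0.5 × 0.8 × 0.5 = 0.20. If e = 0, the loss is zero.

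**Step 3: simulation.** 6,000 trials per row, 45 per arm, a single-visit ANCOVA standing in for the MMRM, D = 0.59. Cells show the mean estimate and power.

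| e | b | f | SAP baseline | True pre-dose baseline | No baseline term |
|---|---|---|---|---|---|
| 0 | 0.5 | 0.8 | 0.59, 89% | 0.59, 89% | 0.59, 78% |
| 0.295 | 0.5 | 0.8 | 0.47, 71% | 0.59, 89% | 0.59, 78% |
| 0.295 | 0.7 | 0.8 | 0.43, 80% | 0.59, 97% | 0.59, 79% |
| 0.59 | 0.5 | 0.8 | 0.36, 47% | 0.59, 89% | 0.59, 80% |

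The formula agrees: 0.59 − 0.5 × 0.8 × 0.295 = 0.472 in the second row, and 0.59 − 0.5 × 0.8 × 0.59 = 0.354 in the last, against 0.363 simulated.

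**Step 4: chance of noticing the early effect.** The SAP names no test, so a two-sided 5% comparison of two means stands in for one.

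| Per arm in the comparison | Early effect 0.295 SD | Early effect 0.59 SD |
|---|---|---|
| 15 | 12% | 36% |
| 36 (0.8 × 45) | 24% | 71% |
| 45 | 29% | 80% |

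The planned table splits patients into three sampling windows, so the numbers in each will be below the total. Under a 5% test, a moderate early effect would usually go unnoticed and the biased model would stand.

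**The case against.** The strongest reply is that the SAP has seen the problem. Section 6.6 names the risk, plans a check and plans a remedy, and the remedy does remove this bias because the early value becomes an outcome instead of a covariate. That stands, and it narrows the fault to the condition on which the remedy depends.

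Other points also stand:
- Keeping a covariate has value. With no early effect, the SAP baseline gives 89% power against about 78% without one. With a moderate early effect and slope 0.7, power is about equal (80% against 79%), though the estimate is still biased. Simply dropping the covariate is not clearly better.
- Every magnitude rests on assumed inputs.
- HP and MDA are not key secondary endpoints (Section 6.3). Section 7 reports concentrations by arm at all timepoints, and the Day 7 CSF model names no baseline term. Marker evidence does not rest on this model alone.

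A reader might infer that the adjustment removes any early drug effect altogether. It does not: only b·f·e is subtracted. The early effect is fully subtracted only if the slope is 1 and every baseline is post-dose.

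A reader might also infer that the check is a non-randomised comparison because it splits patients by sampling time. The documents do not support that. Summaries are by arm, the trial is double-blind, and nothing suggests that sampling time depends on allocation. The sound criticism is low power and no criterion.

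**Conclusion.** The concern holds as a partial, conditional bias. A post-dose baseline attenuates the Day 7 and Day 28 treatment effects if the drug acts on HP or MDA within 48 h in the same direction as later. The loss is 20% of the later effect at the assumed central values, about 4% to 70% over b = 0.3–0.7, f = 0.5–1.0 and e/D = 0.25–1.0, and zero without an early effect. The SAP does not show which of these applies.

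The firm part needs no assumed effect size: the covariate may be post-randomisation, and the remedy depends on evidence that the SAP leaves undefined. The weakness of the check (about 29% or less for a 0.295 SD early effect at up to 45 per arm) rests on the assumed SD units and on equal allocation. This matters for a secondary pharmacodynamic objective; it does not touch the primary endpoint.

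**What to change.** Remove the condition from Section 6.6 and plan one of these before unblinding:

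1. Restrict the baseline covariate to samples taken before the first dose. Handle patients without one by a missing-baseline indicator, or by imputation from covariates confirmed as pre-dose. The TCD imputation in Section 5.1 is not a ready model: it is fitted to baselines from a window within 2 days of first dose, and Section 6.4 says many of those are post-dose. The SAP also does not say that log-CRP and surgical procedure are pre-dose values.
2. Or always fit and report the SAP's own alternative, with the early sample as a separate visit plus the EVD indicator, alongside the adjusted model. Name which of the two leads.

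In either case, change the wording so that the summary of early concentrations describes them and does not claim to confirm that no effect has emerged.

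The cost is SAP wording, one extra model under the second option, and some loss of precision. How much depends on how many patients have a pre-dose sample, which the SAP does not say.
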